### Analysis Plan

At the end of the 6 months, for each participant, the research team expects to have up to 4380 hours of continuous data from the Fitbit Charge 3, 365 EEG segments, 730 daily questionnaires, 7 acceptability questionnaires (BIPQ, SUS, and PSSUQ) and 1 semistructured interview. We also expect that during the study, each participant will have at least 6 seizures, and therefore, the total number of seizures across all patients is expected to be at least 72.

Initially, descriptive statistics will be applied on questionnaires (BIPQ, SUS, and PSSUQ) and demographic information (age, sex, and education) to have an overview of the overall experience. Data missing rate will be also calculated for each device and descriptive analysis will be applied. Using regression analysis, we will investigate if any demographics or other numerical information (sleep, mood, stress) serves as a predictor for participant dropout (if it occurs before the end of the 6 months). We will then estimate for each participant whether there is any relationship between the data missing rate and the self-reported measures (sleep, mood, stress) as well as the monthly acceptability assessment (PSSUQ).

Finally, a thematic analysis will be performed on the recorded semistructured interviews and the weekly call. Audiorecordings will be transcribed, and then a thematic analysis will be performed using NVivo software (version 12; QSR International) by 2 researchers working independently. Initially, the major themes and subthemes will be identified. Once all themes and subthemes are labeled, a secondary analysis will be performed to categorize the dimensions extracted.

The quantitative measures will be computed using data from 3 periods: preictal (within a defined period prior to seizures), postictal (within a defined period following seizures), and interictal (all other times). We will rerun our analysis using 3 different time periods for preictal and postictal periods (24 hours, 72 hours, 7 days); interictal time periods of the same duration as the preictal and postictal periods will be randomly selected from interictal periods approximately equidistant from consecutive seizures. For each peri-ictal period, we will calculate the median of each of the following variables: BNI, variability of NI distribution, mean degree, clustering coefficient, and alpha power shift. We will also calculate the median heart rate, total steps, total sleep hours, mean mood, and mean stress in the 12 hours prior to the EEG measurements.

The primary analysis will be assessed by the area under the receiver operating characteristic curve (AUC) using each of the 5 variables. AUC is the current gold standard for the evaluation of seizure detection and seizure prediction performance.

In an exploratory factor analysis, we will investigate relationships between variables and their independent predictive values using mixed-effects logistic regression models with repeated measurements. For each seizure, the repeated measurements will be the same variables as the primary analysis and the questionnaires (mood, stress, sleep quality, self-assessment of seizure risk, and medication taken) in the preictal, postictal, and interictal periods.

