## Methods

### Study Design and Population

EEG@HOME is an observational nonrandomized and noninterventional study. A total of 12 people with epilepsy referred as part of their routine clinical care to the epilepsy clinics at King’s College Hospital and partner hospitals will be enrolled. Patients will be included if they have received a diagnosis of treatment-resistant epilepsy, their age is between 18 and 75 years, and they experience more than 12 seizures (with impaired awareness) per year according to their seizure diary. A current diagnosis of psychogenic nonepileptic attacks (dissociative seizures), inability to comply with the trial procedure or give informed consent, and the use of other electronic medical devices that could interfere with the data collection will result in exclusion from the study.

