### Study Withdrawal

Participants will be free to withdraw from the study at any time. In the case of participant self-withdrawal, a face-to-face appointment will be scheduled to establish the cause of withdrawal, collect qualitative and quantitative data regarding their experience, and collect the EEG system and equipment. All data, including those from study withdrawals, will be included in the final analysis.

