Through the Seer app, participants will provide a range of patient-reported outcomes with information regarding their mood (twice per day, range of 1-5), stress level (twice per day, range of 1-3), sleep quality (in which participants rate last night’s sleep compared with the previous night, with choices for worse, usual, and better), medication compliance (twice per day, binary yes or no), and seizure events (seizure start, end, and movement) via brief app questionnaires. The questions were selected and adapted to our study from already published studies focused on seizure precipitants and triggers [11,12]. Changes in these patient-reported outcomes that could associate with and potentially predict seizure occurrences will be evaluated.

To provide information about patient characteristics that could determine compliance and feasibility, a set of questionnaires will be administered. Beliefs and attitudes will be assessed using the Brief Illness Perception Questionnaire (BIPQ). It is a validated 9-item scale designed to rapidly assess the patients’ emotional and cognitive illness representations. The questionnaire is structured in 6 sections to assess different factors: consequences (BIPQ 1), timeline (BIPQ 2), personal control (BIPQ 3), treatment control (BIPQ 4), identity (BIPQ 5), concern (BIPQ 6), and emotions (BIPQ 8). Finally, 1 item assesses illness comprehensibility (BIPQ 7) [42].

Two validated questionnaires (System Usability Scale [SUS] and Post-Study System Usability Questionnaire [PSSUQ]) will be used to assess participants’ first impressions after the training and the overall experience of the study, respectively. The SUS is a 10-item usability questionnaire that will be used in this study to evaluate interaction with the ANT Neuro EEG recording system and the Fitbit Charge 3. It is an easy and fast scale to administer and has been validated on small sample sizes with reliable results that allow effective differentiation between usable and unusable systems [43].

The PSSUQ is a short and validated questionnaire that will be used in this study to assess patients’ experiences with the EEG system and the Fitbit Charge 3. It includes 16 items created to measure users’ perceived satisfaction with a system at the end of a study [44]

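### Twelve participants cannot support a regression for predictors of dropout on about six candidate variables; report dropout descriptively instead

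*Protocol article*

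**What the plan says.** The Study Design and Population section fixes the sample: "A total of 12 people with epilepsy". In the Analysis Plan, questionnaires and demographics (age, sex, education) are first summarised, and missing rates are calculated per device. Then comes the commitment at issue: "Using regression analysis, we will investigate if any demographics or other numerical information (sleep, mood, stress) serves as a predictor for participant dropout", qualified by "if it occurs before the end of the 6 months". The article gives no expected dropout and no limit on the number of predictors. It does not say whether predictors enter together or singly, and it does not call the result descriptive.

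Other places bear on this point:

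- The next sentence of the Analysis Plan relates each participant's missing rate to self-reported sleep, mood and stress and to the monthly PSSUQ.
- Data Measured has participants enter mood, stress and sleep quality in the app; the Fitbit also records sleep. It says of the questionnaires: "To provide information about patient characteristics that could determine compliance and feasibility, a set of questionnaires will be administered". BIPQ is one of them, but the Analysis Plan lists it only for descriptive statistics.
- Under Study Withdrawal, "Participants will be free to withdraw from the study at any time". Withdrawing participants are seen to establish the cause, and their data are kept. The final interview described in Data Measured also asks why a device was abandoned.
- Data Security and Privacy has the team check the amount of data per participant every week.

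**The concern.** Method, outcome, candidate predictors and sample size are all stated, and they do not fit together. Dropout is one binary observation per person, so the information is bounded by the smaller of the two groups. In 12 people that is at most 6.

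Feasibility and acceptability are the main goal in Study Objectives, and the results are meant to shape larger home studies. A statement that, say, low mood or age predicts dropout would be carried into the next design. The planned regression would give either no estimate or one too unreliable to carry that weight.

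A second, smaller problem concerns the predictors. App entries exist only while the participant keeps making them. Someone who leaves early contributes a shorter series than a completer, possibly from a different phase of follow-up. If the two groups are summarised over different windows, the comparison mixes the predictor with the time at which it was measured.

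**Working it through.** **Inputs.** N = 12 (Study Design and Population). Predictors: age, sex, education, sleep, mood, stress = 6 (Analysis Plan). The dropout rate is not stated, so I assume 10% to 50%, that is 1.2 to 6 expected dropouts, and show results for d = 1 to 6. No test level is stated; I assume two-sided 0.05. The article gives no figure for this analysis, so there is none to reproduce.

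**1. How many dropouts to expect.** With rate q, P(none) = (1 − q)^12.

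| q | Expected (12q) | P(none) | P(2 or fewer) | Dropouts per predictor (12q/6) |
|---|---|---|---|---|
| 10% | 1.2 | 28% | 89% | 0.2 |
| 20% | 2.4 | 7% | 56% | 0.4 |
| 30% | 3.6 | 1% | 25% | 0.6 |
| 50% | 6 | <0.1% | 2% | 1.0 |

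**2. All six predictors together.** I used 1000 simulated data sets for each d, with n = 12, predictors unrelated to dropout, one of them a 6/6 binary and five normal. A data set counts as non-estimable if a linear combination of the predictors separates dropouts from completers completely or quasi-completely, because the maximum-likelihood logistic estimate is then infinite.

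**3. One predictor at a time.** The same check with a single normal predictor gives the second column below. Power uses the two-group t comparison as a stand-in for the one-predictor model: 10 df, critical value 2.228, noncentrality δ/√(1/d + 1/(12 − d)). For δ = 1 SD the noncentrality runs from 0.957 (d = 1) to 1.732 (d = 6).

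| d | Non-estimable, 6 joint | Non-estimable, 1 continuous | Power, 1 SD | Power, 2 SD |
|---|---|---|---|---|
| 1 | 100% | 16% | 14% | 41% |
| 2 | 97% | 4% | 22% | 64% |
| 3 | 87% | 0.7% | 27% | 77% |
| 4 | 78% | 0.3% | 32% | 84% |
| 5 | 68% | 0.1% | 34% | 87% |
| 6 | 67% | 0.1% | 35% | 88% |

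**4. Smallest attainable exact p.** For a continuous predictor it is 2/C(12,d): 2/12 = 0.167 with 1 dropout, 2/66 = 0.030 with 2, 2/220 = 0.009 with 3. For a binary predictor with an assumed 6/6 split it is 2·C(6,d)/C(12,d): 30/66 = 0.455 with 2, 40/220 = 0.182 with 3, 30/495 = 0.061 with 4. With such a split, sex could not reach 0.05 with 4 or fewer dropouts, even if all were of one sex.

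**5. Six looks.** 1 − 0.95^6 = 0.265, so about a 26% chance of at least one false positive if the tests are independent and hold their nominal level.

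**The case against.** The article does not say that the model is joint. Asking whether any of several variables predicts dropout fits one-at-a-time screening at least as well. A reader might infer that the regression cannot be estimated at all. The text does not support that: a single continuous predictor is nearly always estimable with 3 or more dropouts, and even the joint model is estimable in about a third of simulated data sets with 5 or 6. This part of the objection stands. The two readings need separate verdicts, and both are unfavourable.

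A reader might also infer that sleep, mood and stress are missing exactly when participants disengage, or that they are averaged over a shorter follow-up for dropouts. Neither is stated. Entries made before withdrawal are kept, Fitbit sleep is passive while the device is worn, demographics are unaffected, and the article gives no averaging rule. An article may leave the window to the full plan. What stands is conditional: without an early window common to both groups, the comparison can be biased.

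The Fisher figures concern only an assumed 6/6 binary variable. They show how coarse the data are for sex, not that every predictor is hopeless.

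Much of the remedy is already in the article: reasons for withdrawal are collected, and the next sentence already analyses missing rate. That is a fair point, and it makes the change cheap. Finally, this is a conditional secondary analysis with no stated significance threshold; the primary analysis is the AUC. That limits the severity but does not make the regression informative.

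**Conclusion.** The concern holds in this form: 12 participants cannot support the stated regression, whichever way predictors are entered. Jointly, there is at most 1 dropout per predictor if up to half the cohort leaves, and no finite maximum-likelihood estimate in about 67% to 100% of data sets. Singly, power is about 14% to 35% for a 1 SD difference, with about a 26% chance of a false lead over six independent tests. Only differences near 2 SD with several dropouts would be detected reliably.

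These figures rest on an assumed 1 to 6 dropouts, a logistic model without penalisation, unrelated predictors in the simulation and a two-sided 0.05 level. The point should be corrected because feasibility is the study's main goal. It does not affect the AUC analysis.

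**What to change.** Replace the dropout regression in the Analysis Plan with:

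1. The number of dropouts out of 12 with an exact confidence interval. For example, 3 of 12 gives 5% to 57% (Clopper-Pearson, 95%), which shows how little the sample can say even about the rate.
2. A participant-level listing of dropout time and reason, from the withdrawal appointment and interview already planned.
3. A descriptive comparison of dropouts and completers on baseline characteristics, including BIPQ, and on first-month sleep, mood and stress, so that both groups are summarised over the same window. Anyone who leaves within the first month should be shown separately with the days observed.
4. A sentence saying that no inferential claim about predictors of dropout will be made.

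Any modelling should build on the missing-rate analysis already planned, using the weekly rates already monitored, with a participant random intercept and the label exploratory. There are up to 12 × 26 = 312 participant-weeks if nobody leaves, but they are clustered. Participant-level covariates such as BIPQ still rest on 12 people, and the previous week's self-reports may themselves be missing. This model is optional and does not escape the missing-predictor problem.

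Cost: wording and code, no new data. Downside: no model-based statement about predictors of complete dropout.

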### Data Measured

Electroencephalographic data will be collected using the ANT Neuro eego (approximately 10 minutes of recording while the participant is resting with eyes closed every morning and evening at an interval of approximately 12 hours). First, 1 trained neurologist will visually examine each 10 minutes of EEG recorded, and all the focal interictal epileptiform discharges (IEDs), generalized spike-wave discharges, and focal slowing will be marked. Then, at least one 20-second segment of EEG while the participant is awake with eyes closed that is free of movement and artifacts, signs of drowsiness or sleep, or IEDs will be selected from each recording.

From each segment, different EEG features will be extracted, starting from simple conventional measures to more complex and novel biomarkers. Initially, the power spectra will be calculated. Specifically, our analysis will be focused on 5 frequency bands (1-5 Hz, 6-9 Hz, 10-11 Hz, 12-19 Hz, and 21-70 Hz) defined from previous literature [33,34].

The first measure that will be calculated is the alpha power shift. It is defined as the ratio of average power in the low-alpha power (6-9 Hz) over average power in the high-alpha power (10-11 Hz). Abela and colleagues [35] compared patients with good and poor (4 or more seizures in 12 months) seizure control, showing that alpha power shift is a robust indicator of seizure liability.

In addition, from each 20-second EEG segment, we will infer functional brain networks in which each node corresponds to the brain region underneath each electrode and the edges denote statistical dependencies between the corresponding EEG signals. We will use the phase-locking factor, ignoring all connections at zero lag [36] as well as those that are not statistically significantly different from surrogate data [37]. We will quantify structural properties of the functional brain networks using graph theory metrics, such as the mean and variability of the degree distribution and clustering coefficient [33,38].

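### The 12-hour look-back for mood and stress equals the spacing of both the EEGs and the ratings, so small timing shifts decide whether an EEG gets zero, one or two ratings (minor; exploratory analyses only)

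*Protocol article*

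**What the plan says.** Three statements in the Protocol article interact.

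- **EEG timing (Data Measured):** recordings are made "every morning and evening at an interval of approximately 12 hours".
- **Rating frequency (Data Measured):** the app collects "mood (twice per day, range of 1-5") and "stress level (twice per day, range of 1-3"). No clock times are given, and nothing says whether a rating comes before or after the EEG session.
- **Linkage rule (Analysis Plan):** the covariates attached to each EEG include "mean mood, and mean stress in the 12 hours prior to the EEG measurements". The article gives no rule for a window that contains no rating.

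Two further statements limit what is at stake. "The primary analysis will be assessed by the area under the receiver operating characteristic curve (AUC) using each of the 5 variables", and those five are EEG measures. The peri-ictal analysis uses "3 different time periods for preictal and postictal periods (24 hours, 72 hours, 7 days").

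**The concern.** A look-back window works for sparse, discrete ratings when it is clearly longer than the interval between them. Here the two lengths are nominally equal. If participants use the app around the EEG session, one candidate rating lies near the start of the window and the next near its end, and minutes decide whether each counts.

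Two examples with full compliance:

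- EEGs at 08:00 and 20:30, app completed 20 minutes after each. The evening window opens at 08:30. The 08:20 rating is too early and the 20:50 rating is too late, so the evening EEG has no mood or stress value.
- App at 19:55 and 07:30, EEG at 07:40. The window opens at 19:40, so both ratings count and the mean combines two states about 12 hours apart.

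At stake is the exploratory question in Data Measured of whether EEG features relate to mood or stress. Values could be lost for reasons unrelated to compliance, the age of the linked rating would change from session to session, and the loss could follow time of day.

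**Working it through.** **Inputs from the article.** 2 EEGs per day about 12 h apart; 2 mood and 2 stress ratings per day; 12-h look-back; "up to 4380 hours of continuous data from the Fitbit Charge 3, 365 EEG segments, 730 daily questionnaires".

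**The plan's own counts.** 4380 / 24 = 182.5 days. EEGs: 2 × 182.5 = 365, as stated. Questionnaires: 4 × 182.5 = 730 if mood and stress are counted separately; a single twice-daily form would give 365. Either way there are 365 mood ratings for 365 EEGs, an average of one per window. The question is how they fall.

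**Assumptions (not in the article).** Full compliance; session times normal around 08:00 and 20:00 with SD s; a rating counts if it lies in (EEG − 12 h, EEG].

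**1. Ratings scatter independently around the same times as the EEGs.** Let e be the EEG's deviation from its nominal time, and r0 and r1 the deviations of the previous and current ratings, all from one distribution. The window is empty when r0 < e < r1, one of 3! = 6 equally likely orders: 1/6 = 17%, whatever the SD. Two ratings fall inside when r1 < e < r0, also 17%. Empty: 365 / 6 ≈ 61 EEGs per participant.

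**2. Rating logged 15 minutes (0.25 h) after each EEG.** The current rating is always too late. The previous one is too early when the gap G between EEGs is at least 12.25 h. With G ~ N(12, 2s²):

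P(empty) = 1 − Φ(0.25 / (s√2))

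| s (h) | P(empty) |
|---|---|
| 0.25 | 24% |
| 0.5 | 36% |
| 1 | 43% |
| 1.5 | 45% |

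Simulation agrees. With a delay varying between 10 and 35 minutes and s of 0.5 to 1 h, the simulated share is 30-39%, or about 110-144 of 365.

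**3. Longer daytime gap, rating 15 minutes after, s = 0.5 h.**

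- 13 h by day, 11 h by night: evening Φ(0.75 / 0.707) = 86%, morning 1 − Φ(1.25 / 0.707) = 4%; overall 45%.
- 14 h by day, 10 h by night: evening Φ(1.75 / 0.707) = 99%, morning 0.1%; overall 50%.

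**4. Rating logged 5 minutes before each EEG, s = 0.5 h.** None empty. Two ratings count when G < 12 − 5/60: Φ(−0.083 / 0.707) = 45%.

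**5. Other patterns (simulated).** Ratings at about 12:00 and 18:00 with EEGs at 08:00 and 20:00: 50% empty, all of them morning EEGs. Two ratings at random times from 07:00 to 23:00: 32% empty. EEGs and ratings exactly 12 h apart: 0%. Ratings at about 10:00 and 22:00: 0.2%.

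**6. Whole 24-hour periods.** A 24-h period holds about two EEGs. Simulating the 10-35 minute delay with a daytime gap of 12, 13 or 14 h and s of 0.5 or 1 h, both of two consecutive EEGs are empty in 0.04-8.2% of cases. Six consecutive EEGs (72 h) are essentially never all empty. Under pattern 1 the pair needs one order out of 5! = 120, so 0.8%. The 8% belongs to those settings: with a fixed 15-minute delay and s = 1 h, both gaps must reach 12.25 h with correlation −0.5 between them, which gives about 11%.

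**The case against.** The strongest reply is that the size rests wholly on unstated rating times. That is correct. The share is zero under some ordinary habits, and the figures near 50% need either a daytime gap longer than the stated 12 hours or particular assumed rating times. A reader might infer that about half of all EEGs will lose their mood and stress values; the article does not support that as an expectation, only as a ceiling.

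A second reply is that rating times and the treatment of empty windows belong in the full protocol or SAP, and that 12 hours may loosely mean the preceding half-day. Their absence from the article is indeed no finding. The window length, however, is stated, and read as written it is poorly matched to the sampling.

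Third, a reader might infer damage to the seizure prediction results. The primary AUC uses EEG variables only. The exploratory mixed-effects models take the questionnaires by peri-ictal period, and that sentence does not mention the 12-hour look-back, so they may use the ratings directly. Even if they use the 12-hour values, few periods are empty.

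Fourth, averaging two ratings is what a mean allows. The article does not show that a single value per EEG was intended, so windows with two ratings are not an error. They show only that the content of the variable varies with timing.

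What stands is that the look-back equals the spacing of both series, so for a discrete rating its yield is sensitive to minutes.

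**Conclusion.** The point holds as a minor one. The stated rule can leave fully compliant participants with EEGs that carry no mood or stress value: 0% if each rating is logged just before its EEG, about 17% if ratings vary independently around the same times, about 30-40% if the app follows the EEG at 12-hour spacing, and a ceiling near 50% with a longer daytime gap, where the loss falls mostly on evening EEGs. All but the 17%, which does not depend on the spread, rest on assumed rating times and session variability.

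The effect is confined to the exploratory association of mood and stress with EEG features and to any period summary built from the 12-hour values. The primary analysis is untouched. An uneven weighting of morning and evening ratings could remain in period summaries even where a period is not empty. Losses created by the window should also not be read as non-compliance when the planned missing-data rates are reported.

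**What to change.** For mood and stress only, replace the 12-hour window with the most recent rating before the EEG, up to a maximum age longer than the sampling interval, for example 18 hours. Heart rate and steps are recorded continuously and do not need the change.

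In simulation this brings empty windows to essentially 0% in every pattern where ratings are made near the EEG, and from about 32% to about 10% with ratings at random waking times. It keeps the plan's ordering, in which the rating precedes the EEG. Taking the nearest rating on either side of the EEG would give that up.

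The cost is one sentence in the analysis plan, provided that app entries carry times. The downside is that some linked ratings will be older than 12 hours: these are the EEGs that would otherwise have had no value. Where two ratings now fall in the window, only the later one is used. Reporting the age of the linked rating, by morning and evening, would make this visible.

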**Methods:**

A total of 12 adults with a diagnosis of pharmaco-resistant epilepsy and at least 20 seizures per year will be recruited at King’s College Hospital, London. Participants will be asked to self-apply an easy and portable EEG recording system (ANT Neuro) to record scalp EEG at home twice daily. From each serial EEG recording, brain network ictogenicity (BNI), a new biomarker of the propensity of the brain to develop seizures, will be extracted. A noninvasive wrist-worn device (Fitbit Charge 3; Fitbit Inc) will be used to collect non-EEG biosignals (heart rate, sleep quality index, and steps), and a smartphone app (Seer app; Seer Medical) will be used to collect data related to seizure occurrence, medication taken, sleep quality, stress, and mood. All data will be collected continuously for 6 months. Standardized questionnaires (the Post-Study System Usability Questionnaire and System Usability Scale) will be completed to assess the acceptability and feasibility of the procedure. BNI, continuous wrist-worn sensor biosignals, and electronic survey data will be correlated with seizure occurrence as reported in the diary to investigate their potential values as biomarkers of seizure risk.

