### Study Objectives

The main goal of the EEG@HOME study is to develop and test a feasible and acceptable procedure for people with epilepsy to easily undertake twice-daily, at-home EEG coupled with an event app and continuous data collection from a wrist-worn wearable sensor device. All the information gathered about acceptability and feasibility of the procedure will be published and used to refine methods for future and larger controlled studies at home.

The study will produce a substantial amount of continuous data from people with epilepsy over many months. Assuming complete data collection, we estimate having 60 hours of raw EEG data and 4000 hours of raw wrist-worn sensor data collected at home per participant in addition to patient-reported events. Recognizing the uniqueness of the data set, we will curate it and make anonymized data and clinical metadata available to other researchers, with the aim to create an open database for future research.

The unique set of wearable EEG data, sensor data, and self-reported events will be then analyzed to develop a general model to predict periods of increased seizure risk. The association between self-reported events (seizures, medication taking), sensor data (sleep, heart rate), and EEG features will be investigated within and between subjects.

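### In the exploratory mixed-effects logistic model, sampling periods in sets per seizure leaves a random intercept with little ability to adjust for a person's usual level, so predictors should be split into within-person and between-person parts

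*Protocol article*

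**What the plan says.** The Analysis Plan section of the protocol article defines preictal and postictal windows of 24 hours, 72 hours and 7 days. It takes the comparison windows from the time between seizures: "interictal time periods of the same duration as the preictal and postictal periods will be randomly selected from interictal periods approximately equidistant" from consecutive seizures. The primary analysis is an AUC for each of five EEG variables. An exploratory analysis follows, using a logistic mixed model for repeated measures to examine how the variables relate and what each one predicts on its own. On its data structure the article says: "For each seizure, the repeated measurements will be the same variables as the primary analysis and the questionnaires", in the preictal, postictal and interictal periods.

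The Study Objectives section states the aim: the association between self-reported events, sensor data and "EEG features will be investigated within and between subjects".

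The article does not state the grouping factor, the random-effect structure, whether predictors are centred, how the three periods become a binary outcome, or how many interictal windows are drawn per seizure. It gives no power, alpha or effect size for this model.

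**The concern.** The period labels come from the sampling, as in a matched case-control study. A random intercept in a logistic model describes how the outcome share varies between clusters. If every seizure contributes about the same set of periods, that share hardly varies between participants and the intercept variance goes to zero. The fit is then ordinary pooled logistic regression, although the model's name suggests that repeated measurements have been dealt with.

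The model also assumes that the intercept is unrelated to the predictors. Under set sampling it is not: a participant whose BNI is usually high needs a correspondingly low intercept. When the intercept cannot do this, the slope compares absolute levels across people and does not isolate change before a person's own seizures.

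Two things are at stake. A real within-person signal may be missed in a study with few participants. And because each coefficient shrinks according to that variable's own between-person spread, ranking the variables by coefficient would partly rank them by how much people differ in level.

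**Working it through.** **Inputs from the article.** "A total of 12 people with epilepsy" (Study Design and Population); "each participant will have at least 6 seizures" and "the total number of seizures across all patients is expected to be at least 72" (Analysis Plan).

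**The article's own figure.** The entry criterion in Study Design and Population is "they experience more than 12 seizures (with impaired awareness) per year". 12 per year × 0.5 year = 6 per participant, and 12 × 6 = 72, so the figure reproduces. The Abstract gives "at least 20 seizures per year", which would imply 10 per participant and 120 in total; these two passages need to be reconciled. The check uses 6 per participant.

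**Assumptions not in the article.** One preictal and one interictal window per seizure (1:1); random intercept by participant; uncentred predictor; two-sided 5% likelihood-ratio test. The predictor is x = u + d·(preictal) + e, where the person level u has SD τ and the within-person noise e has SD 1. Ranges: d = 0.4 to 0.6 and τ = 0.5 to 2. The intraclass correlation is τ²/(1+τ²): 0.2, 0.5 and 0.8 at τ = 0.5, 1 and 2.

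**Why the slope shrinks.** Within one person, with 1:1 sets, the log odds of a row being preictal is d·(x − u) − d²/2. The correct slope is d, and the person's intercept contains −d·u, so it is tied to the predictor. Pooled over people, x has variance 1+τ² in both kinds of row, and the slope becomes about d/(1+τ²). For d = 0.5:

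| τ | 0.5/(1+τ²) | simulated median slope, random-intercept model |
|---|---|---|
| 0 | 0.50 | 0.52 |
| 0.5 | 0.40 | 0.42 |
| 1 | 0.25 | 0.27 |
| 2 | 0.10 | 0.11 |

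With the predictor centred on the participant's mean, the simulated slope was 0.56 at every τ.

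**Does the intercept collapse?** Random-intercept models were fitted by maximum likelihood, 200 runs per setting. For d = 0 to 0.6 the estimated intercept SD was zero in essentially all runs. The rejection rate equalled that of ordinary logistic regression wherever both were fitted. In smaller checks (60 runs) with 1:1:1 sets, unequal seizure counts, 20% random missingness, or grouping by seizure, it was zero in 98 to 100% of runs.

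**Power, 12 × 6 seizures, 1:1 sets** (3000 runs, using ordinary logistic regression because of that equality; Monte Carlo SE at most √(0.25/3000) = 0.9 points):

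| d | centred | uncentred, τ = 0.5 | τ = 1 | τ = 1.5 | τ = 2 |
|---|---|---|---|---|---|
| 0.4 | 70.9% | 60.5% | 40.1% | 19.1% | 7.1% |
| 0.5 | 87.0% | 80.2% | 61.8% | 36.9% | 16.8% |
| 0.6 | 94.9% | 91.8% | 80.1% | 57.8% | 32.1% |

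Loss (centred minus uncentred), in points for d = 0.4, 0.5 and 0.6:
- τ = 0.5: 10.4, 6.8, 3.1
- τ = 1: 30.8, 25.2, 14.8
- τ = 1.5: 51.8, 50.1, 37.1
- τ = 2: 63.8, 70.2, 62.8

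**With a postictal row added (1:1:1, preictal against the rest, no postictal effect, 1500 runs).** The loss is 1 to 8 points at τ = 0.5, 7 to 27 at τ = 1 and 49 to 69 at τ = 2. It is smaller in most cells, but not at d = 0.4, τ = 2, where it is 80.9 − 12.2 = 68.7 points.

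**No true effect, τ = 1.** In a separate 300-run simulation the random-intercept model rejected 1% of the time and conditional logistic regression 4.3%.

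**The case against.** **The model is inferred.** The article names neither a random intercept nor uncentred predictors, and an analysis plan not shown may settle both. That is fair, and it is wrong to read the article as prescribing an uncentred random intercept. But the article does fix the sampling and the type of model, and a standard fit of that pair behaves as shown. Richer random effects do not cure it. A correlated random intercept and slope by participant (d = 0.5, 60 runs per setting) gave 65%, 38% and 18% power at τ = 1, 1.5 and 2, identical to pooled regression; centring gave 90%, 83% and 87%. Only centring or conditioning helps.

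**The sets may not be fixed.** A gap must hold a postictal, an interictal and a preictal window, so at least 3, 9 or 21 days. With randomly timed seizures at 12 per year (an assumption), the share of gaps that are too short is 1 − exp(−12 × days/365): about 9%, 26% and 50%. Participants would then differ in their preictal share. In a simulation of this (d = 0.5, at least 6 seizures plus a variable excess, 100 runs per setting), the intercept SD exceeded 0.1 in 55 to 100% of runs at a mean excess of 20 seizures, and in 3 to 53% at a mean excess of 6. Shrinkage persisted, but the loss was 3 to 19 points at τ = 1 and 16 to 59 at τ = 2. This stands as a limit on the size.

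**A reader might infer that the random intercept never has anything to estimate.** That goes too far. Besides the short-gap case, at d = 1.5 and τ = 2 its variance was positive in about 85% of 40 runs.

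**A reader might quote one large loss, such as 20 to 65 points, whenever people differ in level.** The article supplies neither the intraclass correlation nor the effect size, and at τ = 0.5 the loss is small. Six seizures is also a minimum: with 20 per person (d = 0.5, τ = 2, 40 runs) power was 87.5% against 100%, although the slope was still 0.135 against 0.532.

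**The stakes are modest.** The analysis is exploratory, the primary analysis is the AUC, and the study's main goal is feasibility and acceptability. The error is conservative, so it does not generate false positives. All of this stands.

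**Conclusion.** The point holds for the exploratory model, on the reading of about one set per seizure with uncentred predictors. A random intercept is then estimated at or near zero for effects up to about 0.6 SD. The slope mixes level with change and shrinks by roughly 1/(1+τ²), and the test is conservative (about 0 to 1% rejection under no effect when between- and within-person SD are equal).

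The loss of power depends on assumptions: about 3 to 10 points if the between-person SD is half the within-person SD, 15 to 31 if equal and 63 to 70 if double, for 12 × 6 seizures, 1:1 sets and effects of 0.4 to 0.6 SD. It is generally somewhat smaller with 1:1:1 sets or where short seizure gaps make the sets unequal. The documents do not show which of these applies, so no single figure should be quoted as the plan's loss. The finding does not touch the primary AUC or the feasibility aims. It is a cheap improvement to an exploratory analysis.

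**What to change.** Keep the logistic mixed model. Enter each predictor as its deviation from the participant's own mean, and add the participant mean as a separate between-person term, reported descriptively. This serves both halves of the aim in Study Objectives. State the grouping factor, the outcome coding and the number of interictal windows per seizure alongside it.

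Conditional logistic regression stratified by participant or seizure can serve as an alternative or sensitivity analysis; stratified by seizure, its power was within about 2 points of the centred model (200 runs). It should not be the only analysis, because it gives no between-person coefficient.

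The cost is a sentence in the analysis plan and one extra term per predictor, with no new data. The between-person terms will carry little information under this sampling, which is why they should stay descriptive.
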